**Figure 2 F2:**
[figure not shown]
This figure represents a flowchart comprising all the interventions of the TOPAR PILOT trial.

### Number of patients needed

This trial is designed on the basis of a critical appraisal of the existing evidence. The observed difference between the recurrence rates of TPTX+AT and TPTX is of clinical relevance. To assess both methods a multicentred randomized controlled trial is mandatory.

A pilot study design was chosen for the following reasons: In the context of a noninferiority design with a binary primary endpoint using the confidence interval approach for the odds ratio a sample size of 2 × 656 = 1310 patients would be needed to detect non-inferiority with δ = 1588 based on equal risks of recurrence in both groups (or lower in TPTX) with a power of 80% and a significance level of 5% (Monte-Carlo simulation using logistic regression). Incorporating a rate of drop-outs of 15%, 2 × 770 = 1540 patients would be needed. In case of slight differences between the centres the power will not change significantly. Assuming that a risk of 12,5% in the TPTX+AT group is not inferior based on the risk rate of 10% in the TPTX group (difference of 0.025 or an odds ratio of 1.286) would lead to a sample size of more than 4000 and is therefore far from feasibility. The latter margin is the same as usually used for bioequivalence trials (change of 80% or 125%). Therefore better estimates are needed and a pilot multicentred randomized controlled trial comparing 50 versus 50 randomized patients seems feasible and ethical to assess the recurrence rate of both methods after three years in specialized centres.

### Clinical sites

Sites are selected according to their experience in parathyroid surgery and willingness to adhere to the clinical trial protocol. The surgical expertise of each participating surgeon is documented and taken into account during the analysis of the trial data.

### Safety aspects

A small part of each gland is sent to pathology for frozen section in order to confirm organ diagnosis. The success of the intervention is assessed by perioperative monitoring of PTH and calcium recorded in the CRF. All participating centres guarantee cryopreservation of parathyroid tissue from each patient to enable possible subsequent parathyroid autotransplantation, if necessary. If postoperative persistent hypoparathyroidism refractory to medical treatment occurs, reimplantation is performed. The necessity of reimplantation is discussed and defined in each individual case by a medical clinical expert board. Therefore, clinical symptoms (e.g. repeated episodes of paraesthesia and seizures or others), the necessity and amount of medication to achieve normocalcemia and laboratory data (PTH, calcium) will be taken into consideration.

All serious adverse events (SAE) have to be reported to the principal investigator and the leading ethic committee. For the safety analysis the incidence of adverse events (AE) and SAE are analyzed. Patients may be withdrawn from the study at any time either at their own request or at the request of the principal investigator.

Safety evaluation will be done. The adverse events of both treatment groups will be demonstrated in comparison considering severity and causality. Safety interim analyses are planned each year and the independent data and safety board will follow the progress of the trial to control the safety.

### Statistical Analysis

Statistical methods are used to assess the quality of data, homogeneity of treatment groups, endpoints and safety of the TPTX versus TPTX+AT technique. The analysis is performed on the basis of an intention to treat (ITT) population and with respect to ITT principles. A patient belongs to the ITT population, when the patient was found to be suitable for the study, signed the informed consent form and was randomized thereafter.

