**Methods/Design:**

Patients with sHPT (intact parathyroid hormone > 10 times above the upper limit of normal) on long term dialysis (>12 months) will be randomized either to TPTX or TPTX+AT and followed for 36 months. Outcome parameters are recurrence rates of sHPT, frequencies of reoperations due to refractory hypoparathyroidism or recurrent/persistent hyperparathyroidism, postoperative morbidity and mortality and quality of life. 50 patients per group will be randomized in order to obtain relevant frequencies of outcome parameters that will form the basis for a large scale confirmatory multicentred randomized controlled trial.

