**Discussion:**

sHPT is a disease with a high incidence in patients with chronic renal failure. Even a small difference in outcomes will be of clinical relevance. To assess sufficient data about the rate of recurrent sHPT after both methods, a multicentred, randomized controlled trial (MRCT) under standardized conditions is mandatory.

Due to the existing uncertainties the calculated number of patients necessary in each treatment arm (n > 4000) makes it impossible to perform this study as a confirmatory trial. Therefore estimates of different outcomes are performed using a pilot MRCT comparing 50 versus 50 randomized patients in order to establish a hypothesis that can be tested thereafter.

If TPTX proves to have a lower rate of recurrent sHPT, no relevant disadvantages and no higher morbidity than TPTX+AT, current surgical practice may be changed.

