## Methods/Design

### Objectives of the study

The objective of this study is to compare different outcomes of TPTX and TPTX+AT for sHPT over a three-year follow-up period. The information gained will be used for further clinical trials.

The primary objective of this trial is to assess a better estimate of the rates of recurrence of both methods. This shall establish a hypothesis that can be tested thereafter.

Secondary objectives are divided into those occurring intraoperative, postoperative until discharge and after discharge until 36 months postoperatively.

Intraoperative categories comprise the duration of the surgical procedures, the expertise of the responsible surgeon, and complications and findings during surgery.

Within the postoperative setting until discharge, the frequency of persistent hyperparathyroidism, the morbidity and the length of hospital stay are noted. During follow up, the frequency of persistent or recurrent sHPT, the frequency of subsequent parathyroid autotransplantation due to refractory hypoparathyroidism, the frequency of reexploration of the neck or the parathyroid autograft, the frequency of irreversible paralysis of the recurrent laryngeal nerve, the change of symptoms related to sHPT as well as the change in quality of life and finally the incidence of death are recorded.

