### Interventions

#### Preoperative interventions

Patients eligible to participate will be asked to give informed consent. Patients will be randomised into the following treatment groups thereafter.

Consecutively, baseline data will be documented at screening visit, including past medical history, current specific medication and current symptoms of sHPT. A quality of life questionnaire (SF-36) will be handed out preoperatively.

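### One ITT population also governs safety, so in-hospital operative harms are counted without regard to whether surgery took place or which procedure was done; a supplementary table of operated patients would be a cheap improvement

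*Protocol article*

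**What the plan says.** The Statistical Analysis section lists what the statistics are to assess, including "endpoints and safety of the TPTX versus TPTX+AT technique". The next sentence fixes the population: "The analysis is performed on the basis of an intention to treat (ITT) population and with respect to ITT principles". A patient belongs to it who was found suitable, "signed the informed consent form and was randomized thereafter". Surgery is not a condition.

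Randomisation comes before the operation. Under Preoperative interventions, once consent has been sought: "Patients will be randomised into the following treatment groups thereafter". Safety aspects allows withdrawal at any time, which includes the interval before surgery.

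Objectives of the study lists two groups of outcomes that exist only if an operation takes place. The intraoperative group includes "complications and findings during surgery". For the hospital stay: "Within the postoperative setting until discharge, the frequency of persistent hyperparathyroidism, the morbidity and the length of hospital stay are noted".

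Safety aspects and Descriptive analysis say that adverse events will be compared between the treatment groups and that safety endpoints will be described. Neither names another population or grouping rule.

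**The concern.** For harms of the operation itself, the natural denominator is the patients operated on and the natural grouping is the procedure performed. Under the stated rule, a randomised patient who never reaches theatre can sit in the denominator without being able to have the event. A patient who receives the other procedure has any harm credited to the allocated technique.

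Two uses of the results are affected. The pilot randomises 50 patients per group "in order to obtain relevant frequencies of outcome parameters that will form the basis for a large scale confirmatory" trial, so morbidity frequencies are part of its product. The abstract's Discussion also makes "no relevant disadvantages and no higher morbidity than TPTX+AT" one of the conditions for a possible change in practice. For a claim of no greater harm, a contrast pulled towards zero is not conservative: it favours the claim.

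**Working it through.** The plan states no figure on this point, so there is none to reproduce. The check asks how far deviations could move an operative harm rate and the difference between arms.

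**Inputs**

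- Patients per arm: 50 (Abstract, Methods/Design; Number of patients needed).
- Operative harm rates: not given. Assumed pH = 15% and pL = 10% in the higher- and lower-risk arm, a difference of 5.0 points. The article does not say which arm would be which.
- Deviations: not given. Assumed 3 of 50 in one or both arms.
- Unoperated patients stay in the denominator with no operative harm. Crossover patients have the average risk of the procedure they receive.

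**Non-operation.** With u patients not operated on, an arm's ITT rate is p × (50 − u)/50. For u = 3 this gives 15% × 47/50 = 14.1% and 10% × 47/50 = 9.4%.

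**Crossover.** With shares cH and cL crossing over, the ITT difference is (pH − pL) × (1 − cH − cL), where 3/50 = 0.06.

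| Deviation | ITT difference (points) | Shift (points) | Patients per 50 |
|---|---|---|---|
| None | 5.0 | 0 | 0 |
| 3 of 50 unoperated, both arms | 14.1 − 9.4 = 4.7 | −0.3 | 0.15 |
| 3 of 50 unoperated, higher-risk arm only | 14.1 − 10.0 = 4.1 | −0.9 | 0.45 |
| 3 of 50 unoperated, lower-risk arm only | 15.0 − 9.4 = 5.6 | +0.6 | 0.30 |
| 3 of 50 cross over, one arm | 5.0 × 0.94 = 4.7 | −0.3 | 0.15 |
| 3 of 50 cross over, both arms | 5.0 × 0.88 = 4.4 (14.7% v 10.3%) | −0.6 | 0.30 |

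**Other assumptions.** With harm rates of 20% and 10%, and equal shares u unoperated and c crossing over in both arms, the ITT difference is 10 × (1 − u − 2c) points:

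- u = 5%, c = 0: 9.5 points, a shift of 0.25 patient per 50.
- u = 5%, c = 5%: 8.5 points, a shift of 0.75 patient per 50.
- u = 10%, c = 10%: 7.0 points, a shift of 1.5 patients per 50. Here one patient in five deviates.

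If both procedures truly carry a 10% rate and 5 of 50 in one arm are not operated on, ITT shows 10% against 9%, a difference that is not real.

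**Sampling error.** For 15% against 10% with 50 per arm, the 95% half-width is 1.96 × √(0.15 × 0.85/50 + 0.10 × 0.90/50) = 1.96 × √0.00435 = 12.9 points. The exact 95% interval for a single arm with 5 of 50 events is 3.3% to 21.8%.

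**Direction.** Crossover at average risk shrinks the difference. Non-operation shrinks it when equal in both arms or confined to the higher-risk arm, and widens it when confined to the lower-risk arm.

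**The case against.** The strongest reply is that this is an omission in a condensed article. Supplementary analysis sets are commonly left to the full protocol or analysis plan, neither of which is shown, and naming a main population does not exclude others. It stands in part: those documents may well contain a treated-patient set. But the article is not silent. It names safety and endpoints together and then gives one population for the analysis. The point concerns that stated rule.

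It can also be said that the text never explicitly counts unoperated patients in the denominator for intraoperative complications, and that Descriptive analysis asks for counts as well as percentages. A reader who knew how many were operated on could recompute a rate. That would repair the denominator but would not reassign patients who received the other procedure.

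Deviations may be rare. Candidates are already listed for parathyroidectomy, randomisation chooses between two operations, centres are high-volume, surgeons have manuals, and the neck exploration is common to both arms. This stands, and it is why the size is put as probably small. One-sided thymectomy for the reasons given under TPTX Group is part of that procedure and is not a crossover.

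Grouping by procedure performed gives up randomisation where deviations may follow operative findings. Setting unusual combinations aside could also remove the difficult cases from both groups. Both objections stand, and the fix is shaped by them.

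A reader might infer more than the documents support:

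- **That ITT is wrong for safety generally.** It is appropriate for follow-up outcomes and for the overall adverse event table.
- **That the plan will hide excess harm from TPTX.** No harm or deviation rate is given, and the direction depends on which arm is affected.
- **That the 15% drop-out allowance under Number of patients needed bounds the problem.** That figure belongs to a hypothetical confirmatory trial and is not a rate of non-operation.

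**Conclusion.** The point holds as a minor one. As written, the ITT rule covers operative harms, does not require an operation and groups by allocation, so deviations would distort the in-hospital harm rates and usually, though not always, pull the contrast towards zero. The effect is nil without deviations. With 3 of 50 deviating and assumed harm rates of 15% and 10%, it stays under half a patient per 50. Larger assumed deviations give larger shifts: 1.5 patients per 50 in the most extreme case shown, which is 3 points and still well below the 12.9-point half-width calculated for 15% against 10%.

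The consequence is limited further because safety is analysed descriptively, and the main Discussion and the section on surgeon's expertise bias place a confirmatory study before any change in practice. The wording should be improved because doing so is easy, not because a pilot conclusion is at risk.

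**What to change.** Keep ITT for recurrence, the other follow-up outcomes and the overall AE/SAE table. Add to Statistical Analysis:

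*Intraoperative harms and harms until discharge are also reported in all patients whose parathyroid operation was started, by allocated group and by index procedure performed (autotransplantation done or not done).*

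Add a short grouping rule:

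- Every operated patient stays in one of the two groups.
- Deviations in thymectomy and incomplete parathyroidectomy are flagged in the table and not removed.
- Later reimplantation of cryopreserved tissue does not change the group.

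The cost is one sentence, this rule and one extra table. The surgeon already documents the particulars of each operation (Surgical interventions), and no sample size, power or significance level changes. The downside is that the by-procedure comparison is not protected by randomisation and may be confounded by operative findings. It should therefore be labelled supplementary and shown beside the ITT harm table.

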#### Descriptive analysis

Baseline characteristics as well as efficacy and safety endpoints will be analyzed with descriptive methods. The description of continuous variables includes at least: number of observations, mean, standard deviation, median, minimum and maximum in the trial population. The description of nominal variables includes at least the number and percentage of patients belonging to the relevant categories in the trial population as well as in each treatment group. In order to improve the presentation of the observed data, graphical methods will be applied.

### Trial organization, quality control and registration

TOPAR PILOT was designed at the Department for Visceral, Thoracic and Vascular Surgery, Philipps-University, Marburg in cooperation with the Study Centre of the German Surgical Society (SDGC), Heidelberg and the Institute of Medical Biometrics and Informatics (IMBI) at the University of Heidelberg.

Quality assurance will be done in cooperation with the Network of Coordinating Centres for Clinical Trials (KKS).

The trial is monitored by an independent monitor of the KKS in Heidelberg. The trial is performed according to the Declaration of Helsinki in its current German version and the Good Clinical Practice (GCP). Before the start of the trial the independent ethics committee of the Philipps-University, Marburg gave a positive vote on August 21th 2006. The trial was registered on August 22d in 2006 at the International Standard Randomized Controlled Trial Number Registration (ISRCTN86202793).

### Current status and duration of the trial

Up to now, 2 centres are initiated. The first patient was randomized on January 24th 2007. The expected recruitment period will last 18 months.

## Discussion

TOPAR PILOT is a randomized controlled multicentred pilot trial to generate high quality evidence comparing the outcomes of TPTX+AT vs. TPTX. Since secondary hyperparathyroidism is a very common disease in patients with chronic kidney failure, even a small difference in outcomes will be of clinical relevance. If TPTX proves to have no relevant disadvantages and a smaller rate of recurrent sHPT, a large scale confirmatory study will be launched to establish this approach.

Recent reports comparing TPTX+AT to TPTX were retrospective, underpowered or not designed as RCT's. No unique definition for recurrent sHPT was used to calculate the rate of recurrent sHPT. The follow up periods of former studies have often been too short and were not standardized (table 2). Therefore we will perform a follow up of each patient at 6, 12, 24 and 36 months after surgery to allow an assessment of the medium/long term effect of the different surgical treatments.

**Table 2 T2:** Rate of recurrent sHPT after TPTX or TPTX+AT

**Reference**	**TPTX+ AT n**	**TPTX n**	**Routinely performed thymectomy**	**Mean length of follow – up (months)**	**Recurrent sHPT^1 ^(%)**
Rothmund et al. 1991 [29]	20		yes	43	0
Zaraca et al. 1999 [58]	18		no, only if palpation was suspicious or parathyroid gland was missing	28	10
Walgenbach et al. 1997 [46]	67		yes	18	4.5
Walgenbach et al. 1998 [59]	86		yes	24	3.5
Henry et al.1990 [40]	152		no	30	10.5
Welk and Alix 1987 [60]	21		n.m.	33	24
Hampl et al. 1991 [37]	13		yes	33.5	76.5
Chou et al. 2002 [61]	75		n.m.	54	13.3
Bessell et al. 1993 84	42		n.m.	40	9.5
Dotzenrath et al. 2003 [62]	99		yes	51	6
Korzets et al. 1987 [63]	19		n.m.	6–60	26.3
Kinnaert et al. 2000 [31]	59		no	38	12
Tominaga et al. 1997 [39]	519		yes	36	10
				60	20
Ockert et al. 2002 [32]	11		no	38	45
		11	no	22.5	0
Kaye et al. 1993 [64]		13	n.m.	46	0
Higgins et al. 1991 [44]	34		no	72	80
		9	no	10	0
Nicholson 1996 [36]	13		no	24	16
		24	no	24	0
Saunders et al. 2005 [52]		55	no	29	4
Stracke et al. 1999 [35]		20	n.m.	20	4
Hampl et al. 1999 [65]		11	no	26	0
Ljutic D et al. 1994 [66]		43	no	104	2.3

n.m. = not mentioned

^1 ^Recurrent sHPT is defined as an increase of PTH > 5 fold above normal value after more than 6 months after initial PTX and after initial (postoperative) normalization of PTH.

The evaluation of optimal surgical options and procedures should be performed according to the best current knowledge. Due to the principles of Evidence-based Medicine (EbM), the randomized controlled trial is assumed to be the "Gold Standard" in evaluating different medical methods and procedures. Even in RCT's, the risk of bias should not be underestimated. In surgical trials a double blinded trial design is difficult to establish. In this study, even a patient-blinded trial design would necessitate a shame procedure at the forearm for fake autotransplantation in the TPTX-group which is in this case unethical due to the design of a non confirmatory study.

However, the patient selection, power, randomization, surgeon's skill, data assessment and documentation of outcome measures and statistical analysis are important design issues and susceptible to the different forms of bias. Hence, all these issues are specified in the trial protocol a priori.

### Selection bias

To minimize selection bias all patients scheduled for parathyroidectomy because of sHPT are screened consecutively in all participation sites. Moreover, neither patient age nor the amount of PTH-secretion is an exclusion criterion. Screening lists and case report files are monitored by independent investigators from the SDGC to ensure correct patient recruitment and meticulous documentation.

### Randomization bias

Randomization is done using in an internet-based computer randomization. The randomization will be stratified by centres and will be done to generate equal treatment groups by minimizing selection bias. Stratification for the participating clinical sites will reduce bias due to centre effects.

### Surgeon's expertise bias

In this study, stratification for surgeon's skill is made and measured data will be analyzed by analysis of variance in regard to surgeon's skill and centre. Due to this analysis of variance, bias of centre effects and surgeon's skill should be reduced.

The trial will only be performed in high volume centres (defined as more than 15 parathyroidectomies per year for sHPT) minimizing bias due to learning effects. No additional surgical training has to be done as the neck exploration is the same in TPTX as in the standard procedure of TPTX+AT.

In conclusion, this is the first randomized controlled multicentred trial comparing different surgical techniques in parathyroid surgery for sHPT. If significant, the results will be revised by a large scale confirmatory study. The results may change the current surgical practice thereafter.

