#### Postoperative interventions

At day of discharge from hospital, the laboratory parameters and current specific medication are documented again. Patients are asked to fill out another quality of life questionnaire (SF-36). Assessment of vocal cord function has to be documented.

After discharge a follow up visits at 6, 12, 24 and 36 months postoperatively are performed. Follow-up visits consist of a telephone call, a written questionnaire (medical history, current specific medication and specific symptoms and a quality of life questionnaire (SF-36)) to the patient, who is asked to complete it with the help of their general practitioner or nephrologists. The follow up is under the responsibility of the centres under supervision of the SDGC.

Figure 2 shows a flow-chart of the interventions.

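### Adding the preoperative SF-36 score as a covariate to the analysis of variance named for measured data would estimate the quality-of-life arm difference more precisely, at almost no cost.

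*Protocol article*

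**What the plan says.** All references are to the protocol article.

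- **Baseline measurement.** Under Preoperative interventions: "A quality of life questionnaire (SF-36) will be handed out preoperatively".
- **Follow-up measurement.** Postoperative interventions repeats the questionnaire at discharge, then sets the schedule: "After discharge a follow up visits at 6, 12, 24 and 36 months postoperatively are performed". The SF-36 is part of those contacts.
- **Outcome.** Objectives of the study lists, among the secondary items recorded during follow-up, "the change of symptoms related to sHPT as well as the change in quality of life".
- **General analysis.** Under Descriptive analysis: "Baseline characteristics as well as efficacy and safety endpoints will be analyzed with descriptive methods". The summaries listed there are given as a minimum.
- **Named model.** In the Discussion, under Surgeon's expertise bias: "measured data will be analyzed by analysis of variance in regard to surgeon's skill and centre". The stated aim is to reduce bias from centre effects and surgeon's skill. No baseline covariate is named. The logistic regression mentioned under Number of patients needed belongs to a sample-size simulation.
- **Surgeon's skill.** Clinical sites also says that each surgeon's documented expertise enters the analysis.
- **Size.** Number of patients needed settles on 50 per arm: "a pilot multicentred randomized controlled trial comparing 50 versus 50 randomized patients seems feasible and ethical". No quality-of-life hypothesis, target difference or power is given.

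**The concern.** With a baseline and a follow-up measurement of the same scale, there are three usual ways to compare arms: the follow-up score alone, the change from baseline, or the follow-up score adjusted for baseline. In a randomised trial all three estimate the same arm difference, but with different precision. The model named in the article has surgeon's skill and centre as its factors, and the outcome named in the objectives is change. Read together, they bring in the baseline score by subtraction and nowhere else.

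Subtraction treats a one-point difference at baseline as if it carried forward in full. If the correlation is below 1, it carries forward only in part. The change score therefore over-corrects, and part of any chance baseline difference between arms remains in the estimate with its sign reversed. With 50 patients per arm such differences are not negligible.

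What is at stake is limited: the width of the interval around a secondary outcome, in a pilot whose purpose is estimation.

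**Working it through.** **The plan's own figure.** There is none for the SF-36. The only powered calculation concerns a hypothetical confirmatory trial on recurrence: "a sample size of 2 × 656 = 1310 patients would be needed to detect non-inferiority with δ = 1588". Reading the margin as an odds ratio of 1.588, with 10% risk in both arms, one-sided 5% and 80% power, n = 2(1.645 + 0.842)² / [0.10 × 0.90 × (ln 1.588)²] ≈ 643 per arm. This is within 3% of the stated 656. It has no bearing on the SF-36, so the precision check below needs assumptions.

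**Inputs**

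- From the documents: n = 50 per arm.
- Assumed, because the documents do not give them: the same SD at baseline and follow-up, and a correlation ρ between them of 0.3 to 0.7. Results are in units of that SD.

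**Formulas.** The variance per patient, relative to one score, is:

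- change score: 2(1 − ρ)
- baseline-adjusted: 1 − ρ²
- ratio, adjusted to change: (1 − ρ)(1 + ρ) / [2(1 − ρ)] = (1 + ρ)/2

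The ratio is below 1 for every ρ below 1, so the direction does not depend on the value assumed for ρ.

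The 95% interval half-width is 1.96 × √(2/n) × √variance. For n = 50, √(2/50) = 0.200.

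| ρ | Change variance | Adjusted variance | Ratio | Reduction | Half-width, change | Half-width, adjusted |
|---|---|---|---|---|---|---|
| 0.3 | 1.40 | 0.91 | 0.65 | 35% | 0.464 SD | 0.374 SD |
| 0.5 | 1.00 | 0.75 | 0.75 | 25% | 0.392 SD | 0.339 SD |
| 0.7 | 0.60 | 0.51 | 0.85 | 15% | 0.304 SD | 0.280 SD |

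**Baseline imbalance.** 2(1 − ρ) = (1 − ρ²) + (1 − ρ)². The extra term (1 − ρ)² is the variance that chance baseline imbalance contributes. Lost precision and openness to imbalance are thus one cost seen from two sides, and should not be counted twice. For a baseline difference of one standard error (0.200 SD), the change-score comparison shifts by (1 − ρ) × 0.200, which is 0.14, 0.10 and 0.06 SD for ρ = 0.3, 0.5 and 0.7. Adjustment removes this shift when the relation is linear.

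**Fewer evaluable patients.** With 43 per arm (50 × 0.85 = 42.5, rounded up), the half-widths are 0.500 against 0.403 SD, 0.423 against 0.366 SD, and 0.327 against 0.302 SD. The ratios do not change. The 15% loss is borrowed from the confirmatory calculation; the article states no drop-out rate for the pilot.

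**If the analysis of variance were run on follow-up scores instead.** The adjusted-to-unadjusted ratio is then 1 − ρ², or 0.91, 0.75 and 0.51. Adjustment still does better.

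**Cost of estimating the slope.** Allowing for the fitted baseline slope inflates the adjusted variance by about 1 + 1/(2n − 4) = 1 + 1/96, or 1%. This is small against a 15% to 35% reduction. Centre and skill would be in both models, so ρ is strictly the correlation within their levels.

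**The case against.** The strongest objection is that this is a journal article and neither the full protocol nor an analysis plan is at hand. Covariates for a secondary outcome are commonly left to those documents, and nothing in the article excludes a baseline covariate. That stands as a limit: an unseen plan may already contain the adjustment. It does not remove the point, because the article names a model and its factors, and the proposal is to improve that model.

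A second objection is that the sentence sits in a discussion of surgeon and centre bias, names neither the SF-36 nor the treatment arm, and that the main analysis is descriptive. This also stands in part. The sentence covers measured data without exception, which takes in SF-36 scores, but it cannot be read as a full specification of the quality-of-life comparison.

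A reader might infer more than the documents support:

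- *That the baseline score is ignored.* It is not. The outcome is change, so the relevant loss is that of change scores against adjustment.
- *That the quality-of-life comparison is underpowered.* The pilot states no test, target difference or power for it, so power at any chosen effect would describe an analysis that the article does not plan.
- *That the sizing of the confirmatory trial suffers.* The calculation shown uses binary recurrence on the odds-ratio scale, and SF-36 precision does not enter it.
- *That the SD estimate becomes less reliable.* Its relative precision depends essentially on the degrees of freedom, which adjustment barely alters.

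**Conclusion.** The point holds as a minor, optional improvement. The one model named for measured data, applied to the change in SF-36, leaves precision unused that the preoperative score could supply. The direction is certain for any correlation below 1 if the SDs at baseline and follow-up are equal. The size rests on assumed correlations: a variance reduction of 35% at 0.3, 25% at 0.5 and 15% at 0.7, which narrows the 95% half-width by about 0.02 to 0.09 SD with 50 per arm. If the SDs differ, the ratio changes and (1 + ρ)/2 no longer applies exactly. The estimates of recurrence, which are the primary objective, are not affected, and nothing here makes the quality-of-life comparison invalid.

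**What to change.** In Surgeon's expertise bias, add a sentence for the SF-36: each scale is analysed by analysis of covariance with treatment, centre and surgeon's skill as factors and the preoperative score of the same scale as covariate. The adjusted arm difference is reported with its 95% confidence interval next to the descriptive change in each arm.

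Surgeon's skill should stay in the model, because both this section and Clinical sites say it is taken into account. The outcome can remain the change named in the objectives: once the preoperative score is a covariate, modelling the change or the follow-up score gives the same adjusted arm difference.

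The cost is one extra parameter per scale and a change of wording. No new data, visits or patients are needed. If the full protocol or analysis plan already includes this covariate, it is enough to bring the article's sentence into line with it.
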